#### 3.2 Objectives

The pilot trial will have objectives to:

- Assess the feasibility of study setting, eligible criteria, intervention, outcome measurements, participant timeline and recruitment strategies
- Explore the blinding credibility and the acceptability of the trial

- Determine the adequate sample size for a definitive full-scale RCT
- Preliminary estimate the add-on efficacy and safety in the treatment group (FZHFZY+ urea cream) compared to that in the control group (Placebo+ urea cream).
- Obtain detailed qualitative feedback on experience and acceptability of patients who complete the pilot RCT.

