## 5.6 Outcome measures

### 5.6.1 Trial feasibility

- The proportion of involvement by the number of screened, eligible and consenting participants, as well as the time requirement to recruit eligible participants will be used to assess the feasibility of the study setting, eligible criteria and recruitment strategies
- The compliance rate of using trial medications and the acceptability question will be used to quantitatively evaluate the feasibility and acceptability of the trial [44]
- Blinding credibility at week 4, week 8 and week 20
- Determine the primary outcome and provide data for sample size calculation in the full-scale trial

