### 5.6.2 Efficacy outcomes

#### 5.6.2.1 Primary outcome

- Mean change in the PASI total score from baseline to week 8 and week 20 respectively [45]

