## 5.9 Statistical methods

### 5.9.1 Sample size calculation

Since this is a pilot study, a sample size calculation is not performed. The pilot study aims for 60 participants because a pilot study with at least  $n = 50$  is advisable in many circumstances at a high level of confidence [56], considering a 15% loss to follow-up.

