### 5.9.2 Quantitative data analysis

Statistical analysis will be performed in a blinded manner by qualified statisticians using PASW Statistics 25.0 (IBM SPSS Inc., Armonk, New York, USA). All statistical tests are two-sided with a  $P$  value of  $<0.05$  being considered statistically significant.

Efficacy analyses will be based on the intention-to-treat (ITT) population and safety analyses will be based on the safety analyses set population, both of them defined as all randomised patients who received at least one dose of study treatment and the data of at least one visit. Missing data will be replaced using the multiple imputation method for ITT analysis. For the outcome variables, continuous data (e.g. mean change in PASI score, BSA, itch VAS, and DLQI) will be summarised as mean and standard deviation (data with normal distribution) or mean and interquartile range (data without normal distribution), and categorical data (e.g. PASI-50, PASI-75, and relapse rate) will be summarised as counts and percentages. The primary analyses for primary and secondary outcome variables will be based on the ITT population approach, using data collected at baseline, week 8 and week 20.

When outcome variables are continuous data, using an independent  $t$ -test (data with normal distribution) or Mann-Whitney  $U$  test (data without normal distribution) compares the difference between two groups. When outcomes variables are categorical data, using the Chi-squared test (total samples  $\geq 40$  and expectation  $\geq 5$ ) or Fisher's exact test (total samples  $<40$  or expectation  $<1$ ) compares the difference between the two groups. The efficacy outcomes will be assessed by a generalised linear mixed model for repeated measures.

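### Non-normal continuous outcomes are to be summarised by a mean with an interquartile range, probably a slip for median, and the rule leaves the SD out of the planned summary of a pilot that is meant to inform the full trial's sample size

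*Protocol*

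**What the plan says.** Section 5.9.2 gives two alternative summaries for continuous outcomes, chosen by distribution. If normal, they are "summarised as mean and standard deviation (data with normal distribution"; if not, "mean and interquartile range (data without normal distribution". The two are joined by *or*, so the second replaces the first. The examples named are change in PASI, BSA, itch VAS and DLQI. The same section compares non-normal outcomes between arms with the "Mann-Whitney $U$ test (data without normal distribution". No median is planned anywhere in the protocol.

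Three other places bear on this:

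- Section 3.2 lists as an objective: "Determine the adequate sample size for a definitive full-scale RCT".
- Section 5.6.1 lists as a feasibility outcome: "Determine the primary outcome and provide data for sample size calculation in the full-scale trial".
- Section 5.6.2.1 defines the primary efficacy outcome as "Mean change in the PASI total score from baseline to week 8 and week 20 respectively".

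**The concern.** There are two separate faults in the one sentence.

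First, the pairing. The quartiles describe spread around the median. In skewed data the mean does not sit at the middle of the distribution, and a reader given a mean with two quartiles cannot tell where the middle is. The median is the usual partner, and its absence makes a slip of the pen the likeliest explanation.

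Second, the SD becomes conditional on normality. A trial planned on a mean difference needs the SD of the change whatever its shape. The pilot's own primary outcome is a mean change, and section 5.6.1 leaves the full trial's primary outcome still to be chosen, so every continuous candidate could be called on. Correcting mean to median would cure the first fault and leave the second.

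What is at stake is modest: an awkward descriptive table, and a published summary that omits a planning input which the pilot says it will provide.

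**Working it through.** **The plan's own figure.** Section 5.9.1 states: "The pilot study aims for 60 participants". It rests on at least 50 participants and 15% loss. 50 / (1 − 0.15) = 58.8, so 59; and 60 × 0.85 = 51, which is at least 50. The figure of 60 holds, and nothing in this point disturbs it.

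**What each branch of the rule delivers.**

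| Outcome judged | Centre | Spread | Test | SD in the summary? |
|---|---|---|---|---|
| Normal | mean | SD | t-test | yes |
| Non-normal | mean | interquartile range | Mann-Whitney U | no |

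Sections 3.2 and 5.6.1 place no normality condition on the sample-size input. The second row therefore does not supply in its summary what those sections ask of the pilot.

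**Size, under assumptions.** The protocol gives no SD or distribution for PASI change, so this only shows scale. Assume:

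- a gamma shape with parameter k (mean k, SD √k, skewness 2/√k);
- a true difference of 0.5 SD, two-sided alpha of 0.05 and 80% power;
- a planner who has only the reported quartiles and takes SD ≈ IQR / 1.349, which is exact for normal data.

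With the true SD, n per arm = 2 × (1.960 + 0.842)² / 0.5² = 62.8, so 63. With the substitute SD, 62.8 is multiplied by r², where r = (IQR / 1.349) / SD. True power at the resulting n is Φ(0.5 × √(n/2) − 1.960).

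| Skewness | Mean / median | r | n per arm | Shortfall from 63 | True power |
|---|---|---|---|---|---|
| 0 (normal) | equal | 1.000 | 63 | none | 80% |
| 1.0 (k = 4) | 4.000 / 3.672 = 1.09 | 0.954 | 62.8 × 0.910 = 57.2, so 58 | 5/63 = 8% | 77% |
| 1.4 (k = 2) | 2.000 / 1.678 = 1.19 | 0.908 | 62.8 × 0.824 = 51.8, so 52 | 11/63 = 17% | 72% |
| 2.0 (k = 1) | 1.000 / 0.693 = 1.44 | 0.814 | 62.8 × 0.663 = 41.6, so 42 | 21/63 = 33% | 63% |

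Over this range the mean exceeds the median by 9% to 44%, and a sample size rebuilt from the interquartile range is 8% to 33% too small.

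**Would the non-normal branch be reached?** The protocol does not say how normality is judged. If a Shapiro-Wilk test at 0.05 were used in an arm of 25 to 30, simulation (1,000 samples per setting) put the chance of being declared non-normal at 37% to 45% for skewness 1.0 and 93% to 97% for skewness 2.0. At such skewness, the branch is a realistic one.

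**The case against.** The strongest reply is that section 5.9.2 describes a table and not the source of the full trial's sample size. Neither section 3.2 nor section 5.6.1 ties the planning input to that table. The team holds the individual data, so an SD can be computed at any time, and the mixed model in section 5.9.2 also yields variance estimates. All of this stands. A reader might infer that the pilot will be unable to supply an SD, or that the full trial will be undersized. The documents support neither: nowhere do they propose deriving an SD from quartiles, and the shortfall above needs that step.

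It is also fair to say that the efficacy outcomes are defined as mean changes, so keeping the mean for skewed data has some logic, and that the Mann-Whitney test is not in general a test of medians. That weakens any complaint of a mismatch with the test. It does not explain why an interquartile range should appear without a median, or why the SD should disappear when the mean is retained.

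A reader might also reach for a log-normal model and report a far larger shortfall. That is a poor model here: a change from baseline can be zero or of either sign, and improvement cannot exceed the baseline score. The milder shapes above are the more cautious illustration, though they too are only assumed.

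Finally, it would be too strong to say that the pilot exists to supply this SD. Sample size is one of five objectives in section 3.2.

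**Conclusion.** The point holds as a minor correction. The sentence is a stated rule, not a matter left to a later analysis plan, and taken literally it is wrong on the pairing and at odds with the sample-size objective. The SD is omitted from planned reporting, not lost.

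Any harm to the full trial requires both that outcomes are judged non-normal and that someone plans from the reported interquartile range. In that case the shortfall would be roughly 8% to 33% for skewness of 1 to 2, under the assumptions set out above; for normal data it is nil. The pilot's 60 participants, its analysis populations and its tests do not change.

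**What to change.** In section 5.9.2:

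1. Replace mean by median in the summary for non-normal data, so that it reads median and interquartile range.
2. Add that n, mean and SD per arm will be reported for every continuous efficacy outcome (PASI, BSA, itch VAS, DLQI and Skindex-16) at weeks 8 and 20, whatever the distribution.

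A confidence interval for the SD of PASI change would help whoever plans the full trial, but it is optional.

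The cost is one reworded sentence and a few extra entries in the summary tables. No further data are needed.

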## 5.2 Randomisation and Blinding

A total of 60 eligible participants will be randomly assigned at a 1:1 ratio to one of the two groups at the baseline visit. The equal randomisation will be conducted by the staff at the Key Unit of Methodology in Clinical Research (KUMCR) of the GPHCM who is independent of the trial investigators. Only the person has access to the results of randomised allocation. The random allocation sequence will be generated through the blocked randomisation method using the SAS software (version 9.2, SAS Institute, Inc., Cary, NC, USA). Then the randomisation code corresponding to the trial medications will be released by the Interactive Web Response System for Chinese Medicine Trials that is a verified online randomisation facility established by the KUMCR (<http://59.42.21.236:8088/randomisation/portal/portalLogin>). Therefore, the allocation concealment will be ensured.

The participants, trial investigators, outcome assessors, the statistician, and the pharmacist who dispense medications will be blinded to the allocation. The randomisation code can be broken if the appropriate management of the patient in medical emergencies necessitates knowledge of the treatment randomisation. It should be applied by the trial investigator through the online randomisation system and then the principal investigator will be notified to approve of breaking the code. Therefore, the type of trial medications (CHM or placebo) will be identified. In addition, the reason, date, and result of breaking the randomisation code will be recorded in the patient's case report form. Any condition resulting in an unblinding event will report to the ethics committee of the GPHCM. Breaking the randomisation code under medical emergencies should not spread to ensure the clinical trial continues. If a patient's treatment is unblinded by the investigator, the patient will be withdrawn from the study.

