##### 5.4.1.2 Outcome measures and visits

- PASI, BSA, sPGA and itch VAS: Participants will be evaluated these measures at week 0, 2, 4, 6, 8, 12, 16 and 20
- DLQI and Skindex-16: Evaluate these measures at week 0, 8, and 20
- 11-point ordinal scale: Evaluate it at week 8 and 20
- Blinding credibility: Evaluate it at week 8 and 20
- Chemical examinations: Evaluate electrocardiograms at the baseline, and collect blood (two 4 ml-EDTA tubes and two drying tubes) and urine (one 10 ml-urine tube) at week 0, 8 and 20
- Photos taken for representative skin lesions: Conduct it at each visit
- Concomitant medication, and AEs: Record it during the whole trial phase

- Dispense and collect trial drugs: Dispense trial drugs at week 0, 2, 4, and 6; collect trial drugs at week 2, 4, 6 and 8
- Dispense and collect home diary record sheet: Dispense it at week 0, 2, 4, 6, 8, 12, and 16; collect it at week 2, 4, 6, 8, 12, 16 and 20

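### Section 5.9.2 gives each continuous efficacy outcome two unranked analyses, one of them a test on change without baseline adjustment whose form depends on an unspecified normality check

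*Protocol*

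**What the plan says.** The primary efficacy outcome (section 5.6.2.1) is the mean change in total PASI from baseline, at week 8 and at week 20. Section 5.9.2 sets out the analysis in these steps:

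- **Two-group test.** "When outcome variables are continuous data, using an independent" t-test is used for normally distributed data and a Mann-Whitney U test otherwise. No covariate is mentioned, and nothing says how normality is to be judged.
- **Model.** The same section ends: "The efficacy outcomes will be assessed by a generalised linear mixed model for repeated measures". Its covariates and its standing relative to the two-group tests are not given.
- **Data used.** The primary analyses of primary and secondary outcomes follow the intention-to-treat population, "using data collected at baseline, week 8 and week 20". Missing data are to be multiply imputed.
- **Summaries.** Continuous data that are not normal are described by the mean with the interquartile range.
- **Level.** "All statistical tests are two-sided", with P below 0.05 "being considered statistically significant".

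For PASI, BSA, sPGA and itch VAS, section 5.4.1.2 states: "Participants will be evaluated these measures at week 0, 2, 4, 6, 8, 12, 16 and 20". DLQI and Skindex-16 are measured only at weeks 0, 8 and 20. Section 5.6.1 makes it a purpose of the pilot to supply data for the full-scale sample size.

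**The concern.** Three features of the stated plan cause the difficulty.

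First, change in PASI at week 8 or week 20 can be reported from a two-group test or from a mixed model. The two can disagree, and the text does not say which is to be believed.

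Second, the two-group test is itself chosen after looking at the data. If the check points to Mann-Whitney, the analysis no longer estimates the mean change that section 5.6.2.1 defines as the outcome.

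Third, the two-group test leaves out baseline PASI, which is recorded for everyone. The resulting effect estimate is noisier than it need be, and the SD of change is larger than the SD that a baseline-adjusted full-scale trial would need for its sample size.

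Separately, the mean paired with an interquartile range is a poor summary of skewed data, because it combines a centre that is sensitive to skewness with a quantile-based spread.

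**Working it through.** **Inputs from the protocol.** "A total of 60 eligible participants will be randomly assigned at a 1:1 ratio to one of the two groups" (section 5.2), so 30 per arm; two-sided 0.05 (section 5.9.2). On the sample size, section 5.9.1 says "Since this is a pilot study, a sample size calculation is not performed"; it rests on at least 50 participants with 15% loss. That figure reproduces: 50/(1 − 0.15) = 58.8, rounded up to 59, and 60 × 0.85 = 51, which is at least 50.

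**Assumptions.** The protocol gives no SD, no effect size and no correlation r between baseline and follow-up PASI. I take r from 0.3 to 0.8 and equal variances s² at baseline and follow-up.

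**Cost of not adjusting for baseline.** Per-patient variances are:

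- change score: 2s²(1 − r)
- baseline-adjusted: s²(1 − r²)
- ratio: (1 − r²)/[2(1 − r)] = (1 + r)/2

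The 95% half-width for 30 per arm is 1.96 × √(2 × variance/30), in units of s.

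| r | change | adjusted | ratio | excess SE, change score | 60 adjusted patients equal | half-width, change → adjusted |
|---|---|---|---|---|---|---|
| 0.3 | 1.40 | 0.91 | 0.65 | 24% | 60/0.65 = 92 | 0.60 → 0.48 |
| 0.5 | 1.00 | 0.75 | 0.75 | 15% | 60/0.75 = 80 | 0.51 → 0.44 |
| 0.6 | 0.80 | 0.64 | 0.80 | 12% | 60/0.80 = 75 | 0.45 → 0.41 |
| 0.7 | 0.60 | 0.51 | 0.85 | 8% | 60/0.85 = 71 | 0.39 → 0.36 |
| 0.8 | 0.40 | 0.36 | 0.90 | 5% | 60/0.90 = 67 | 0.32 → 0.30 |

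The sixth column is the number of patients the change-score test would need to match 60 analysed with adjustment.

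The direction does not depend on equal variances. With baseline SD s0 and follow-up SD s1, change-score variance minus adjusted variance is s0² + s1² − 2r·s0·s1 − s1²(1 − r²) = (s0 − r·s1)², which is never negative (large samples, linear model).

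**How often two analyses give two answers.** I simulated 4,000 trials per setting with 30 per arm. The t-test or Mann-Whitney test on change was chosen by Shapiro-Wilk, and ANCOVA stood in for a baseline-adjusted mixed model.

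- Normal data, assumed effect 0.6 SD: the two disagreed on significance in 24%, 18% and 9% of trials at r = 0.3, 0.5 and 0.7.
- No effect: at least one was significant in about 7–8% of trials.
- The check sent about 10% of truly normal data sets to Mann-Whitney.
- Skewed (log-normal) data, with r on the log scale and a 0.6 effect on the rescaled score: t-test and Mann-Whitney disagreed in 12–17% of trials. Power for Mann-Whitney against ANCOVA was 63% v 70%, 76% v 75% and 93% v 88% at r = 0.3, 0.5 and 0.7.

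**Value of the intermediate visits.** I compared generalised least squares variances for the treatment difference with 15% monotone dropout, under compound-symmetry (0.5, 0.7) and autoregressive (0.95, 0.90 per week) correlations. Eight visits gave 0.97 to 0.99 of the three-visit variance, a gain of 1–3%.

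**The case against.** The best defence is that the closing sentence of section 5.9.2 names the efficacy model and the preceding tests are general two-group comparisons. That reading is possible, but the text does not state it, and two analyses of the same outcomes without a ranking remain.

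It can also be said that an unadjusted comparison of change is valid under randomisation and matches the declared outcome, that covariate lists belong in a statistical analysis plan, and that a pilot makes no confirmatory claim. The first and third points stand: the loss is one of efficiency, and the 7–8% figure is not a confirmatory error rate. The second stands for the mixed model, whose covariates are open. It does not cover the two-group test and the switch, which the protocol itself fixes. An adjusted SD could be computed from the collected data whichever test is reported, but nothing in the text says it will be.

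Three stronger readings are tempting and should not be drawn:

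- **That the t-test or Mann-Whitney test is the designated primary analysis.** The text attaches its primary analyses to the intention-to-treat population and to three time points, not to a test.
- **That restricting to weeks 0, 8 and 20 biases the result.** Multiple imputation is stated, and nothing keeps the intermediate visits out of the imputation model. Comparing three-visit and eight-visit models without imputation, under assumed PASI-driven dropout of 15–25%, the week-20 shortfall was from nil to (1.19 − 1.12)/1.19, about 6%. That comparison does not test the stated plan. For DLQI and Skindex-16 there are no further visits to use.
- **That the stated test loses power in every case.** With skewed data Mann-Whitney matched or exceeded ANCOVA at r = 0.5 and 0.7. The objection there is the change of estimand.

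**Conclusion.** The point holds as a matter of ranking, estimand and precision. Section 5.9.2 should say which analysis is the main one, and a data-driven move from a mean difference to a rank comparison does not fit an outcome defined as a mean change. Adjusting for baseline would reduce the variance of the PASI contrast by 15–25% at r = 0.7 to 0.5, and by 10–35% over r = 0.8 to 0.3. These sizes rest on an assumed r and equal variances; the direction does not.

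Because required sample size is proportional to variance, the same ratio applies to the full-scale trial if that trial adjusts for baseline. Sizing it on the change-score SD would then overstate the number needed. The harm is to the estimates carried forward, not to the validity of the pilot. The visit restriction is a minor matter, worth about 1–3% of variance. The summary statistic for skewed data needs correcting on any reading.

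**What to change.** In section 5.9.2:

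- Name one main analysis for PASI: a mixed model for repeated measures with treatment, visit, treatment-by-visit, baseline PASI and baseline-by-visit. Report the week-8 and week-20 differences with 95% confidence intervals, since both belong to the primary outcome.
- Use the same form for BSA and itch VAS, and baseline-adjusted models for DLQI and Skindex-16 at weeks 8 and 20.
- Remove the normality-triggered choice, or keep the rank test as a labelled sensitivity analysis.
- Replace the mean by the median beside the interquartile range for skewed data.
- State that the baseline-adjusted SD goes forward to the full-scale sample size.
- Allow the intermediate PASI, BSA and itch VAS visits into the model or the multiple imputation, as a small gain.

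The cost is a few reworded sentences. All the data are already scheduled for collection, a repeated-measures mixed model is already planned in the named software, and trial conduct does not change.

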## 6. Part 2: The nested qualitative study

The procedure of the qualitative study is presented in Figure 2.

[figure not shown]

**Figure 2** Flowchart of the qualitative study procedure

### 6.1 Study setting

The study will be set in a quiet clinic room of the GPHCM. Participants who have completed the Pilot RCT will participate in the qualitative study. Eligible participants will be provided additional informed consent.

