|-------------------|------------------------------------------------------------------------------------------------------------------------------------------------------------------------------------------------------------|
|                   | functions), vital signs (heart rate, body temperature, respiratory rate and blood pressure), and physical examinations at week 0, week 8 and week 20                                                       |
| Sample size       | 60 participants                                                                                                                                                                                            |
| Trial duration    | Visit 1: The screening date
Visit 2: Baseline (Week 0)
An 8-week treatment period: Visit 3 – Visit 6 (Week 2, 4, 6, 8)
A 12-week follow-up period: Visit 7 – Visit 9 (Week 12, 16, 20)            |
| Qualitative study |                                                                                                                                                                                                            |
| Participants      | Eligible criteria 
 
• Completing the pilot RCT
 
• Willing to participate in qualitative interviews
 
• Written informed consent is provided
 
 |
| Outcomes          | Obtain detailed qualitative feedback on individual therapeutic evaluation and acceptability of the intervention, as well as their experience with the whole trial                                          |
| Sample size       | 24 – 30 eligible participants                                                                                                                                                                              |
| Trial duration    | Within 4 weeks after the end of the pilot RCT, visit 1                                                                                                                                                     |

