The CHM formula *Fu zheng he fu zhi yang* (FZHFZY) was developed by [name], an experienced clinician of Chinese medicine in dermatology, and has been used as an external application for over decades to manage psoriasis symptoms [30, 31]. The formula has been patented by China National Intellectual Property Administration (No. ZL 2018 1 0749464.0) [32]. As observed in clinical practice, the CHM ingredients of FZHFZY exert the clinical benefit of enhancing the overall health, promoting the healing of skin lesions and relieving pruritus. The pre-clinical study has revealed that 19 potential bioactive compounds were discovered and 13 of them were identified in FZHFZY by three cell lines fishing combined with liquid chromatography-mass spectrometry analysis [30]. The FZHFZY formula regulates epidermal differentiation through inhibition of the Akt/mTORC1/S6K1 pathways [33], which offers important insight on how the FZHFZY formula may benefit patients with psoriasis. In addition, the contents of eight active compounds of the CHM formulation were determined by ultra-performance liquid chromatography, which can be helpful for the quality control of FZHFZY [34]. However, the effect and safety of the formula has not been evaluated by a rigorous randomised controlled trial (RCT). Therefore, we designed the study protocol of a double-blinded, placebo-controlled RCT and will conduct a pilot RCT to explore the feasibility of the protocol. Additionally, the experience and acceptability of patients who participate in the trial will be collected with an embedded qualitative interview [35, 36]. Results from the study will optimise a full-scale study design.

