### 3. Aims and objectives

#### 3.1 Aims

The study will assess the feasibility of the trial protocol qualitatively and quantitatively, and preliminary estimate the add-on efficacy and safety of CHM formula FZHFZY external application to topical urea cream for patients with mild-to-moderate psoriasis vulgaris. Results from the pilot study will optimise the study design.

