### 6.2 Participant selection

Interview invitation will be provided when participants complete the pilot RCT of the FZHFZY Trial. We will maximise participant diversity in terms of age, gender, civil state, education level, employment status, geographical location, history and severity of psoriasis vulgaris, comorbidity, response to treatment, AEs, treatment adherence and satisfaction scores from the pilot RCT without knowing their group allocation. Within this context, we seek to achieve diversity in the sample to ensure that a broad range of views, characteristics and experiences of participation will be obtained [57, 58].

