### 6.3 Data collection

Data collection will be performed through qualitative, semi-structured interviews with an interview guide of open-ended questions. It will be conducted within 4 weeks after completing the pilot RCT. During the interviews, participants will be encouraged to speak freely about their efficacy and safety

evaluation and experience with CHM external application for psoriasis vulgaris. Subsequently, they will primarily be asked about their experiences with and perspectives on the entire pilot FZHFZY RCT, and the acceptability of the pilot RCT. We will use the interview guide and questions flexibly to respond to the participant's pace and experience. It means each participant will be encouraged to tell the story in the best suitable way. The duration of the interviews will range from one to one and half hours. We will make field notes during each interview and summarise these at interview completion. With participants' permission, interviews will be audio-recorded and transcribed verbatim.

An interview guide (Table 4) will be developed based on a review of the relevant academic literature addressing similar questions and psoriasis patients' experience of using Chinese herbal medicine [59-63].

**Table 4** Interview guide and interview questions

| Interview guide                                                                                                       | Interview questions                                                                                                                                                                                                                                                                                                                                                                                                                                                                                                                                                                                                                                                             |

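### Interviews are open only to participants who complete the 20-week RCT, so the interview findings on acceptability cannot include anyone who leaves early

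*Protocol*

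**What the plan says.** Completion of the RCT is the entry condition for the interviews in every place that deals with it:

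- Synopsis, qualitative study: the first eligibility criterion is "Completing the pilot RCT".
- Section 3.2: the qualitative objective is "Obtain detailed qualitative feedback on experience and acceptability of patients who complete the pilot RCT".
- Section 6.1: "Participants who have completed the Pilot RCT will participate in the qualitative study".
- Section 6.2: "Interview invitation will be provided when participants complete the pilot RCT of the FZHFZY Trial".
- Section 6.3, on timing: "It will be conducted within 4 weeks after completing the pilot RCT".

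Two statements are wider. The Background says that "the experience and acceptability of patients who participate in the trial will be collected with an embedded qualitative interview". Section 6.2 also asks for a diverse sample, naming response, AEs, adherence and satisfaction among the factors, so that varied experiences of taking part are heard.

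The aim in section 3.1 reads "The study will assess the feasibility of the trial protocol qualitatively and quantitatively", so the interviews are one of the two routes to the feasibility conclusion. The sample size of 60 in section 5.9.1 is set "considering a 15% loss to follow-up".

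**The concern.** The pilot is meant to show whether a daily home bath for eight weeks, eight clinic visits and repeated specimen collection can be carried into a full-scale trial. The fourth part of the interview guide (Table 4) asks about bath temperature, duration, frequency, length of treatment and visits. People who left because of any of these could say most about them, and the entry rule means they are never asked.

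The interviewed group is selected on having stayed for 20 weeks, and staying is plausibly related to finding the trial acceptable. Data saturation (section 6.4) does not correct this, because it would be judged only among completers. The full-scale design could then be settled on a favourable picture of burden, with little structured information on why people leave. Neither retention nor reasons for withdrawal appears among the feasibility outcomes in section 5.6.1.

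**Working it through.** **Inputs from the protocol**

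- Randomised: 60, allocated 1:1 (section 5.2).
- Target of at least 50, with 15% loss to follow-up (section 5.9.1).
- Interviews: 24 to 30, final number by saturation (section 6.4).
- Acceptability: weeks 8 and 20 (Table 1). Section 5.4.1.2 lists an 11-point ordinal scale at the same two visits; I read this as the acceptability question.
- Medication usage check: weeks 2, 4, 6 and 8 (Table 1).

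**Step 1. The plan's own figure.** 50 / (1 − 0.15) = 58.8, rounded up to 59. The stated 60 agrees with this and gives 30 per arm. The 24 to 30 interviews come from no formula, so there is nothing to reproduce there.

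**Step 2. How many the rule excludes.** 60 × 0.15 = 9 outside the interviews; 60 − 9 = 51 inside. The interviews would cover 24/51 = 47% to 30/51 = 59% of completers and 0% of leavers. Actual loss may differ, so the range under assumed rates is:

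| Assumed loss | Cannot be interviewed | Completers |
|---|---|---|
| 5% | 3 | 57 |
| 10% | 6 | 54 |
| 15% (planned) | 9 | 51 |
| 20% | 12 | 48 |

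**Step 3. What an open rule would give.** As an illustration only, since the design is purposive, suppose interviewees were drawn at random from all 60, with 9 leavers among them. The expected number of leavers is 24 × 0.15 = 3.6 to 30 × 0.15 = 4.5. The chance of drawing none is C(51,24)/C(60,24) = 0.6% for 24 interviews and C(51,30)/C(60,30) = 0.1% for 30. Under the written rule the number is always zero.

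**Step 4. What other data leavers contribute, by time of leaving**

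| Source | Leaves before week 8 | Leaves between weeks 8 and 20 |
|---|---|---|
| Screening, eligibility, consent, recruitment time (5.6.1) | yes | yes |
| Medication usage check (Table 1) | at visits attended | complete |
| Acceptability question (Table 1, 5.4.1.2) | none scheduled | week 8 rating |
| Feedback on trial medications (5.5) | optional | optional |
| Interview (6.1 to 6.3) | no | no |

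Someone who leaves before week 8 therefore has neither an interview nor an acceptability rating. Section 6.2 uses satisfaction scores from the RCT as a sampling factor; if these are the acceptability ratings, such a person could not be placed on that factor even if interviews were opened to them, unless a rating is taken at exit.

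**The case against.** The strongest defence is that this is a deliberate scope. Objective 3.2 limits the qualitative aim to completers, the eligibility rule matches it, and the interview covers the whole trial, which only someone who went through all of it can describe in full. It is true that the objective and the rule agree. But the Background and the sampling goal in 6.2 are wider than that objective, and experience of a trial that someone left is still experience of taking part.

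Three stronger readings are tempting, and the documents do not support them.

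- A reader might infer that all acceptability and feasibility findings leave out those who stopped. Recruitment and compliance measures do not need completion, blinding credibility is scheduled at week 4 (Table 1, section 5.6.1), and anyone leaving during follow-up has already reached the week 8 rating. Section 5.5 also lets investigators take feedback from people who withdraw. That feedback is optional, confined to trial medications and tied to no analysis, so it answers the point only in part.
- A reader might infer that the rule removes everyone with poor adherence, adverse events or low satisfaction. The protocol does not define completion. Someone who stopped bathing but attended to week 20 may count as a completer, section 5.3.1.2 describes reasons to suspend or stop the bath without saying that the person leaves the trial, and 6.2 actively samples on these factors. The rule thins the low end rather than removing it. Participants with serious adverse events may be an exception, if section 5.5 is read as ending participation for the individual.
- A reader might take the nine as people who left because the trial was unacceptable. The 15% is a planning allowance for loss from any cause, so nine is an upper bound for that group at the planned rate.

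**Conclusion.** The point holds for the interviews, and for the acceptability rating of anyone who leaves before week 8. Followed as written, the plan gives interview findings drawn wholly from people who stayed: about 9 of 60 excluded at the planned loss, or 3 to 12 at an assumed 5% to 20%.

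The expected direction is towards a too favourable view of acceptability. That rests on the assumption that at least some early leaving is related to burden, tolerability or dissatisfaction. It is likely but not certain, and the documents give no acceptance rates from which a size of bias could be derived.

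The randomised comparison is unaffected. What is weakened is the qualitative half of the feasibility aim, through a criterion that is easy to change and belongs in the protocol and the interview consent.

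**What to change.** 1. In the synopsis, 3.2 and 6.1 to 6.3, replace the completion criterion with *randomised in the pilot RCT*, keeping participation voluntary and subject to the separate interview consent. This also brings the objective into line with the Background. Section 6.6 follows automatically, since the pilot interviews use the same criteria.
2. In 6.2 and 6.3, invite those who leave early at the time of leaving, with the interview within 4 weeks of that date. Completers keep the present window.
3. Add completion status to the purposive sampling factors in 6.2, within the existing 24 to 30 interviews. No fixed quota is needed: the final number is set by saturation, and with about nine leavers a quota might not be filled.
4. In Table 1 and 5.4.1.2, add the existing 11-point acceptability question at early exit.
5. State what counts as completing the RCT, in particular whether someone who stopped the baths but attended week 20 does. The completion status in item 3 needs this definition.

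The cost is an amendment to the protocol text and the interview consent. The number of interviews and the RCT analysis stay the same. Leavers may be harder to reach and some will decline; reporting how many were invited and how many agreed would show how far the gap was closed.
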